### Patient recruitment

As infants need to be enrolled within the first week of life, efforts will target pregnant women. Institutional Review Board (IRB)-approved flyers will be used to recruit pregnant women to participate in the study from the UC Davis Family Practice Center, UC Davis Obstetrics & Gynecology offices, and the inpatient Labor and Delivery ward.

### Study inclusion and exclusion criteria

#### Inclusion criteria

Healthy newborn infants between 1 and 7 days old with intent to be exclusively breastfed for a minimum of 6 months

#### Exclusion criteria

Infants given dietary supplementation, including other probiotics.Infants born prior to 34 weeks gestation.Infants below 10^th^ percentile for body weight.Postnatal use of antibiotics (oral, intramuscular, or intravenous) by either the mother or the infant. Of note, prenatal maternal Group B streptococcus prophylaxis is not a criterion for study exclusion.Family history of immunodeficiency syndrome(s).Infants with signs of a clinically apparent underlying immunodeficiency.Intent to use non-breast milk infant formula for feeding during the first 6 months.History of gastrointestinal tract abnormality or infection.

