Entry into the study requires the intent to breastfeed exclusively for a minimum of 6 months. If mothers decide to discontinue breastfeeding during the study, we will note that in the infant’s notes and obtain an additional series of weekly stool samples for 6 weeks after discontinuation of breastfeeding. The purpose of this additional stool sample collection is to determine if discontinuation of breastfeeding has an impact on the level of existing *B. infantis* colonisation in the infant gut.

A table of the schedule of study visits and specimen collections is provided in Table 1, and an overview of the timeline of the study interventions and assessments is provided in Table 2.

**Table 1 Tab1:** Schedule of study visits and specimen collections for each infant and mother

Week	Visits and activities
Prior to starting the study	• The patients’ parents or legal guardians will be asked to read and sign the consent form and will be instructed on the procedures for collection and storage of stool samples. They will be asked to refrain from giving the child any other dietary supplementation or probiotics while in the study and to inform the researchers if they are prescribed oral antibiotics at any time during the study.
Week 1	• Initial study visit, adverse event survey administration to parents and administration of first dose of *B. infantis* or placebo on day 7 of life.
	• Week 1 stool samples collected (infants will have stool samples collected twice weekly for the first 6 weeks and then at the study visits at weeks 6, 24, 36, 52, and 78).
	• If breastfeeding is discontinued at any point in the study, an additional series of six weekly stool samples will be collected following discontinuation in addition to the regularly scheduled collections
	• Mother collects breast milk on day 7 of life.
Week 2	• Study visit, adverse event survey administration to parents and administration of second dose of *B. infantis* or placebo on day 14 of life.
	• Week 2 stool samples collected
	• Mother collects breast milk on day 14 of life.
Week 3	• Week 3 stool samples collected
	• Adverse event survey administration to parents
Week 4	• Week 4 stool samples collected
	• Adverse event survey administration to parents
Week 5	• Week 5 stool samples collected
Week 6	• Study visit, adverse event survey administration to parents.
	• Week 6 stool sample collected.
	• Mother collects breast milk on day 42 of life.
Week 17	• Mother collects breast milk on day 120 of life.

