### Study-wide number of subjects

We propose a maximum sample size of 90 infants. Five infants (three to receive *B. infantis* supplementation and two to receive placebo) will be enrolled for the initial dose of *B. infantis*. An additional five infants will be enrolled at each dose escalation. Once the pharmacologically effective dose (ED) of *B. infantis* has been reached, two additional dose escalations will be performed (for reasons as described above). We estimate that the ED of *B. infantis* will be identified within seven dose escalations (35 infants). Accounting for the final two dose escalations will bring the total to 45 infants. Following the final dose escalation, 45 additional infants (27 to receive *B. infantis* and 18 to receive placebo) will be enrolled to screen for lower-frequency adverse events using Hanley’s Rule of Three [21]. This will bring the maximum enrollment number to 90 infants. If the ED of *B. infantis* required to produce 50 % gut colonisation at 6 weeks is not reached, then enrollment will be halted after 90 infants have been enrolled. Additional stopping rules are listed in the “Study Endpoints” section.

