## Study endpoints

### Primary outcome measures

#### *Identification of pharmacologically effective dose (ED) of* B. infantis

The primary endpoint of the study is identification of the ED of *B. infantis*, i.e. the dose required to produce predominant (>50 %) gut colonisation at 6 weeks of age. The value of 50 % colonisation was chosen because *B. infantis* represented greater than 50 % of the gut microbiota in the vast majority of Bangladesh infants [19]. The percent gut colonisation will be determined through analysis of stool samples by 16S sequencing.

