### Withdrawal of subjects

Subjects may be withdrawn without their consent if they acquire medical issues during the study period that require administration of oral or parenteral antibiotics or immunosuppressive medications. If a subject is to be withdrawn, the parent(s) will be contacted and the reason(s) for withdrawal will be explained in full. No further data will be collected from withdrawn subjects.

Subjects have the right to withdraw from the study at any time for any reason. Every effort will be made to follow-up subjects who discontinue placebo or *B. infantis* supplementation prior to the second dose. These evaluations should continue according to the protocol of scheduled study visits if at all possible. The reasons for discontinuation will be recorded in the subjects’ study file. If a subject is unable to return for evaluation, every effort will be made to contact via telephone 28 days after withdrawal to determine if any serious adverse events have occurred while off study. Any identified adverse events will be followed until resolution.

The investigator also has the right to remove subjects from the study without their consent. Possible reasons for removal include:Non-compliance with the study protocolSignificant protocol deviationSerious adverse event potentially related to study treatment

Subjects that withdraw after the 6 week study visit will not be replaced with new subjects.

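### After entry, the antibiotic reporting instruction and the withdrawal rule are narrower than the entry exclusion, so some courses can go unrecorded before the week-6 effective-dose reading

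*Protocol article*

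**What the plan says.** Three places in the protocol article deal with antibiotics.

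- **Exclusion criteria.** An infant is not eligible after "Postnatal use of antibiotics (oral, intramuscular, or intravenous) by either the mother or the infant". Maternal prophylaxis for Group B streptococcus before birth is exempt. The entry window is set under Inclusion criteria: "Healthy newborn infants between 1 and 7 days old with intent to be exclusively breastfed for a minimum of 6 months".
- **Table 1, row before the start of the study.** Parents are asked "to inform the researchers if they are prescribed oral antibiotics at any time during the study".
- **Withdrawal of subjects.** For antibiotic use after entry the rule reads: "Subjects may be withdrawn without their consent if they acquire medical issues during the study period that require administration of oral or parenteral antibiotics"; immunosuppressive drugs are treated in the same way. The section then states: "No further data will be collected from withdrawn subjects".

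The reading at stake is the primary endpoint, the ED: "the dose required to produce predominant (>50 %) gut colonisation at 6 weeks of age". Group size is given under Study-wide number of subjects: "Five infants (three to receive *B. infantis* supplementation and two to receive placebo) will be enrolled for the initial dose". Each escalation adds five more infants.

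**The concern.** By barring antibiotics in mother or infant, by three routes, the protocol itself treats them as incompatible with a clean colonisation result in a breastfed infant. It applies that full scope only at entry. Doses are given on days 7 and 14, and colonisation is judged at week 6 (day 42 in Table 1). The exposure most able to disturb the reading therefore falls in the five weeks after the first dose (42 − 7 = 35 days), and there the rules are weaker.

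This is mainly a question of data capture. Eligibility, the instruction to parents and the withdrawal rule belong to the protocol, and the article prints all three. An analysis plan can decide how to handle exposed infants, but it cannot recover exposures that nobody was asked to report. With three active infants per dose, one unrecognised exposure is a large share of the evidence for that dose.

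**Working it through.** **Scope of the three rules**

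| Rule | Whose antibiotics | Route | Force |
|---|---|---|---|
| Exclusion criteria | mother or infant | oral, intramuscular, intravenous | bars entry |
| Table 1 instruction | unclear: parents or child | oral only | report |
| Withdrawal of subjects | the infant | oral or parenteral | discretionary withdrawal, then no data |

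**What the Table 1 instruction misses.** The pronoun in the instruction can be read three ways.

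- Parents: all of the infant's courses and the mother's parenteral courses are outside the request.
- Child: all of the mother's courses and the infant's parenteral courses are outside it.
- Both: parenteral courses in either are outside it.

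On every reading the request omits parenteral courses, although the withdrawal rule acts on them in the infant. On every reading a maternal course after entry has no stated consequence.

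**Timing.** Entry is possible from day 1 to day 7. If the exclusion is applied once, at enrolment, an infant enrolled on day 1 is screened for about one day of exposure and one enrolled on day 7 for about a week. A maternal course on day 5 excludes an infant enrolled on day 6. For an infant enrolled on day 1, the text states no consequence. No re-check before the day-7 dose is described.

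**Size.** The protocol gives no antibiotic rate, so there is no figure of its own to reproduce. Inputs:

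- active infants per dose group: 3 (Study-wide number of subjects);
- probability p that a mother-infant pair has any course between entry and week 6: an assumption, 2% to 15%, with independence between infants.

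Probability that at least one of three active infants is exposed: 1 − (1 − p)³.

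- p = 0.02: 1 − 0.98³ = 1 − 0.941 = 0.059
- p = 0.05: 1 − 0.95³ = 1 − 0.857 = 0.143
- p = 0.10: 1 − 0.90³ = 1 − 0.729 = 0.271
- p = 0.15: 1 − 0.85³ = 1 − 0.614 = 0.386

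One exposed infant is 1/3 of the group's active data. Because p pools mother and infant and all routes, it includes courses that Table 1 asks about or the withdrawal rule can act on. The probability of an unrecorded exposure is therefore smaller than these figures at any given p.

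**The case against.** A reader might infer that the same confounder is excluded before entry and then counted into the ED. The documents do not support that. An infant who receives oral or parenteral antibiotics may be withdrawn and then gives no further data, so an infant withdrawn before week 6 has no week-6 value to count. For maternal courses, being counted is an inference from silence. Which infants enter the ED reading may be settled in the full protocol or analysis plan, neither of which is shown.

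Further points on the other side:

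- **Other channels may reveal some courses.** The monitoring section promises weekly questionnaires in the first month and one at week 6, with evaluation of any illness or infection. An infant ill enough for injected antibiotics would probably come to notice. This stands for the infant. It helps little with a maternal course while the infant is well.
- **Strict entry with discretionary withdrawal is an ordinary choice.** It is, and the difference in force is not the fault. The mismatch in person and route remains, because reporting is narrower than the rule that depends on it.
- **The exclusion has no printed end date.** It could be meant to run up to the first dose. If so, saying so costs one sentence.
- **The effect on the ED is not shown.** The protocol states no rule for combining three infants and gives no effect of maternal antibiotics on infant colonisation. It cannot be claimed that one exposed infant would make an adequate dose look inadequate. The percentages count exposure, not harm to the reading.
- **Excluding and replacing exposed infants would be a poor remedy.** It removes infants after randomisation for an event that might be related to treatment, and it needs arm-matched replacements in a blinded group of five. This stands, and the fix does not ask for it.

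**Conclusion.** The concern holds as a mismatch between three printed rules. The reporting instruction (oral only, person unclear) and the withdrawal rule (infant only, discretionary) are narrower than the entry criterion, which may itself be applied as early as day 1 with no stated re-check. Maternal courses, and parenteral courses that no one is asked to report, can go unrecorded before the week-6 ED reading.

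The mismatch is certain from the text, but its effect is not. At an assumed exposure of 2% to 15%, between 6% and 39% of three-infant active groups would contain at least one exposed infant, and this is an upper bound on what goes unrecorded. The documents show neither that exposed infants are counted into the ED nor that a dose would be misjudged. The correction is worth making because it is nearly free and because unrecorded exposures cannot be recovered later. By the Trial status section, recruitment had not begun.

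**What to change.** 1. Reconcile Table 1, Exclusion criteria and Withdrawal of subjects on whose antibiotics and which routes they cover. Whether maternal use after entry should lead to withdrawal is a clinical decision for the sponsor; the text should state the answer.
2. Reword the Table 1 instruction to any antibiotic, by any route, in mother or infant. Record the dates on each existing survey up to week 6, asking about the period since the previous survey. Table 1 lists surveys in weeks 3 and 4 that Table 2 does not; asking about the interval works under either schedule.
3. Re-check the antibiotic exclusion before the first dose. A baseline survey at that point is already planned. Table 2 places allocation ahead of week 1, so the text should say how the slot is refilled if an infant is found ineligible after assignment, keeping the group at three to two.
4. Prespecify a sensitivity reading: each dose group's week-6 colonisation with and without antibiotic-exposed infants. Show any infant withdrawn for antibiotics before week 6 as missing. With one exposed infant in the active arm, the second reading rests on two infants and should be described as such.

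Cost: wording in three places, one survey item, and an occasional infant found ineligible before the first dose. No change to the dose groups or the maximum of 90 is needed, provided such infants are not counted as enrolled.

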### Protocol for calculating the starting dose of *B. infantis* and dose escalation

Previous studies of *B. infantis* supplementation in premature infants at the UC Davis neonatal intensive care unit (NICU) have used a dose of 1.4 × 10^9^ colony-forming units twice daily for 2 weeks without any observed serious adverse effects [22]. Applying a safety factor of three and adjusting for once-daily dosing yields, a MSRD of 0.9 × 10^9^ colony-forming units of *B. infantis* is to be administered on day 7 and day 14 of life. Each group of five infants will be enrolled at least 2 weeks apart to allow for sufficient time to identify possible adverse events prior to each dose increase. A modified Fibonacci-based dose escalation protocol will be applied as shown below:$$ {F}_n={\displaystyle \sum_{k=0}^{\left[\frac{n-1}{2}\right]}}\left(\begin{array}{c}\hfill n-k-1\hfill \\ {}\hfill k\hfill \end{array}\right) $$

The specific modified-Fibonacci series will be as follows:

×, 2×, 3×, 5×, 9×, 12×, and 16× (where × = 0.9 × 10^9^ colony-forming units of *B. infantis*)

Based on the schedule for enrolling new groups every 2 weeks, by the time the pharmacologically effective dose (ED, defined as the dose of *B. infantis* resulting in 50 % gut colonisation at 6 weeks of age) has been identified, two additional dose escalations will have been performed in successive infant groups. Figure 1 provides schematic representation of infant group enrollment as well as the dose escalation protocol to identify the ED for *B. infantis* as well as the MaxED, if applicable.

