**Fig. 1 Fig1:**
[figure not shown]
A parallel-group, placebo-controlled, randomised, double-blind ascending dose phase I study of dietary supplementation with *B. infantis.* Groups of healthy infants will receive increasing doses of *B. infantis* until it comprises 50 % of their gut microbiota, defined as the pharmacologically effective dose (*ED*). This figure arbitrarily designates Group 6 as receiving the ED of *B. infantis*. After the ED has been reached, two additional dose escalations will occur to determine the impact that additional *B. infantis* has on the gut microbiota. To satisfy Hanley’s Rule of Three, 30 infants will receive the highest dose of *B. infantis*. “*X*” represents the maximum recommended starting dose (*MRSD*). A modified Fibonacci Series (X, 2X, 3X, …) is used to guide the dose escalations. *CFU* colony-forming units

Study visits will be scheduled for weeks 1, 2, 6, 24, 36, 52, and 78. Parents will complete surveys at each study visit to monitor the infants for potential adverse events associated with probiotic administration including feeding intolerance, fevers, or bowel irregularities including constipation and diarrhoea.

Stool samples will be collected twice weekly for the first 6 weeks of life then once weekly at weeks 24, 36, 52, and 78. Stool samples will be analysed to determine the relative abundance of *B. infantis* over time, and the overall diversity of the gut microbiota with and without *B. infantis* supplementation. Stools will also be analysed for milk oligosaccharides to verify consumption of breast milk and to correlate the proportion of human milk oligosaccharides and free sugar monomers seen in the infant stool at various levels of *B. infantis* colonisation.

Breast milk will be collected at 7, 14, 42, 120, and 180 days after the birth of the infant to determine the type and proportion of milk oligosaccharides present at various time points. The purpose of this analysis is to allow correlation of the type and amount of milk glycans present in breast milk with that in the infant stool samples.

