Week 24	• Study visit, adverse event survey administration to parents.
	• Week 24 stool sample collected.
Week 25	• Mother collects breast milk on day 180 of life.
Week 36	• Study visit, adverse event survey administration to parents.
	• Week 36 stool sample collected.
Week 52	• Study visit, adverse event survey administration to parents.
	• Week 52 stool sample collected.
Week 78	• Study visit, adverse event survey administration to parents.
	• Week 78 stool sample collected.

**Table 2 Tab2:** Schedules for study participant enrolment, interventions and assessments in parallel-group, placebo-controlled, randomised, double-blind ascending dose phase I study of dietary supplementation with *B. infantis*

	Enrolment	Allocation	Post-allocation											
Timepoint	–t_1_	0	Week 1	Week 2	Week 3	Week 4	Week 5	Week 6	Week 17	Week 24	Week 25	Week 36	Week 52	Week 78
Enrolment:														
Eligibility screen	X													
Informed consent	X													
Allocation		X												
Interventions:														
Dose #1 of *B. infantis*/placebo			X											
Dose #2 of *B. infantis*/placebo				X										
Infant stool collection			X	X	X	X	X	X		X		X	X	X
Breast milk collection			X (Day 7 of life)	X (Day 14 of life)				X (Day 42 of life)	X (Day 120 of life)		X (Day 180 of life)			
Assessments:														
Identification of pharmacologically effective dose (ED) of *B. infantis*								X						
Study visit			X	X				X		X		X	X	X
Adverse event survey			X	X				X		X		X	X	X
Analysis of stool oligosaccharides			X	X	X	X	X	X		X		X	X	X
Analysis of stool microbiota			X	X	X	X	X	X		X		X	X	X
Analysis of breast milk oligosaccharides			X (Day 7 of life)	X (Day 14 of life)				X (Day 42 of life)	X (Day 120 of life)		X (Day 180 of life)			

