#### Safety

An additional primary endpoint is to determine the safety of *B. infantis* supplementation in immunocompetent, full-term infants. Any adverse events including fever of 38.9 °C (102 °F) or higher, abdominal pain or colic, blood or purulence in the stool, diarrhoea or vomiting will be documented and dosing adjusted accordingly (“Stopping rules” are defined below).

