### Provisions to monitor data and ensure safety of subjects

Children will be recruited for this study. Subjects will be monitored clinically during the study period to assess for potential adverse events. A previous study of *B. infantis* supplementation in premature infants administered similar doses and was well tolerated with no severe adverse events noted [22]. Nonetheless, patients enrolled in the study will be monitored closely and any evidence of feeding intolerance, illness, or infection will be thoroughly evaluated. A survey to assess for any baseline feeding intolerance or symptoms will be administered to all infants prior to administration of *B. infantis* or placebo. Additional symptom questionnaires will be administered weekly during the first month of the study and at every study visit therafter at 6, 24, 36, 52, and 78 weeks. Patients will be provided with the contact information for the principal investigator and on-call dermatology resident should any unforeseen symptoms or problems arise.

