### Rules for stopping dose escalation and halting trial

Dose escalation will be stopped if a maximally tolerated dose (MTD) of *B. infantis* is reached. The data safety monitoring board will evaluate the adverse events reported at each ascending dose of *B. infantis*. If the safety monitoring board deems that one or more of the three infants in the *B. infantis* supplementation group experienced an adverse event (such as fever >38.9 °C (102 °F), abdominal pain or colic, blood or purulence in the stool, diarrhoea or vomiting) then additional dose escalation will be halted.In the event dose escalation is halted due to adverse events, an additional group of five infants will be enrolled with three infants at the same (i.e. not escalated) dose of *B. infantis* and two receiving placebo.If no adverse events occur in this additional, non-escalated group, then dose escalation will be resumed beginning with the next group of enrolled infants.However, if adverse events are noted in one or more infant(s) in the non-escalated group, all further dose escalation will be halted. The *B. infantis* dose will be de-escalated to the previous value, and an additional group of five infants (three *B. infantis*, two placebo) will be enrolled. If no adverse events occur in the de-escalated group, this dose will be considered the MTD and the trial will be stopped.If any adverse events are noted in the de-escalated group, further de-escalation and enrollment of infants will occur to identify the dose of *B. infantis* considered to be the MTD, in which no adverse events occur in the study group.

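### Two weeks between enrolments does not secure a survey after the second dose, or a board review, before the next dose level starts, and the halt rule does not cover groups already at a higher dose

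*Protocol article*

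**What the plan says.** The section on the starting dose and dose escalation spaces the groups so that they are "enrolled at least 2 weeks apart to allow for sufficient time to identify possible adverse events prior to each dose increase". The 2 weeks are a minimum, but Study design and the end of the dose-escalation section both plan on a group every 2 weeks. The latter relies on it: by the time the effective dose (ED) is read at 6 weeks of age, "two additional dose escalations will have been performed in successive infant groups".

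Doses are given on days 7 and 14 of life, and the inclusion criterion admits infants aged 1 to 7 days.

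The survey schedule is given in more than one way:
- Provisions to monitor data: "Additional symptom questionnaires will be administered weekly during the first month of the study".
- Table 1 lists an "adverse event survey" at weeks 1, 2, 3, 4 and 6. The week-2 survey is at the visit where the second dose is given. Weeks 3 and 4 carry no day of life.
- Study design (text after Figure 1): "Parents will complete surveys at each study visit". The visits are at weeks 1, 2, 6 and later. Table 2, as extracted, marks surveys at those weeks and none at week 3 or 4.

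On acting on events, the Safety endpoint says that they "will be documented and dosing adjusted accordingly" and points to the stopping rules. Those say: "The data safety monitoring board will evaluate the adverse events reported at each ascending dose". An event in an active infant halts further escalation and leads to a repeat group at the same dose. If that group is clear, "then dose escalation will be resumed beginning with the next group of enrolled infants".

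**The concern.** The interval has a stated purpose, a safety look before each dose increase, but it is measured on a clock that does not track exposure. What matters is the time from the previous group's second dose to the next group's first higher dose, and whether a scheduled look and a board decision fall in between. Neither is fixed.

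The halt rule also reads as if no higher group were under way, while the dose-escalation section plans for two to be under way by week 6. If an event is first reported once a higher level has started, the rule stops further escalation but does not say whether doses still due at that level are given. The infants concerned are 1 to 2 weeks old, and safety is one of the two primary endpoints.

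**Working it through.** **Inputs.** Doses on days 7 and 14; entry ages *a* (earlier group) and *b* (later group) from 1 to 7 days, so 49 pairs; spacing *S* = 14 days. Each group is treated as entering on one day. The pair counts are not probabilities unless entry ages are uniform.

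**Formulas, on the earlier infant's day-of-life scale.**
- Next level: dose 1 on day 7 + S + a − b, dose 2 on day 14 + S + a − b.
- Two levels up: replace S by 2S.

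**The plan's own figure.** At equal ages and S = 14, the next level has dose 2 on day 28 and the level two up has it on day 42. Three levels up would start on day 7 + 42 = 49. So two escalations are done by day 42, as the article states.

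**Time after the second dose.** The next level's dose 1 falls on day 21 + a − b, that is day 15 to 27. After the earlier infant's dose 2 on day 14, that is 7 + a − b days: 7 at equal ages, range 1 to 13 (each extreme is one pair).

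**Which survey comes first.** The week-2 survey (day 14) precedes the higher dose in 49 of 49 pairs, but it is taken at the dose-2 visit and so covers dose 1 only. For week 3 the answer depends on a day that the article does not give:

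| Assumed day of week-3 survey | Higher dose before survey | Same day | Higher dose after survey |
|---|---|---|---|
| 21 | 21/49 | 7/49 | 21/49 |
| 18 | 6/49 | 4/49 | 39/49 |
| 15 | 0/49 | 1/49 | 48/49 |

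For example, at day 18 the dose comes first when b − a is 4, 5 or 6, which gives 3 + 2 + 1 = 6 pairs; b − a = 3 gives 4 pairs.

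**On the sparser schedule** (Table 2 and the visit-based text) the first survey after dose 2 is week 6. The next level's dose 2 falls on day 28 + a − b, that is day 22 to 34, so that level is fully dosed before day 42 in 49/49 pairs. The level two up has dose 1 on day 29 to 41, so it has also started in 49/49.

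**With S = 21.** The next level's dose 1 falls on day 22 to 34, after a day-21 survey in 49/49. Two levels up, dose 1 falls on day 43 to 55, so that level has not started by day 42 in any pair.

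**The case against.** Several points on the other side are sound.

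- **There is a look before each increase.** The week-2 survey follows 7 days of exposure to the first dose in every pair. Parents have contact details for the principal investigator and an on-call resident, and illness or feeding intolerance is to be evaluated. A reader might infer that the higher dose starts with no safety information at all; the article does not support that.
- **Day 21 is an assumption.** A reader might infer that the higher dose always begins on or before the first survey after dose 2. That is not documented: the count depends on the survey day and falls to 0 of 49 at day 15.
- **Overlap is declared.** Having two higher levels under way at week 6 is the stated design, and an ascending-dose trial need not clear all follow-up before each step. The week-6 counts alone do not show that the interval fails its purpose. They matter because the halt rule has no branch for the overlap.
- **The article is condensed, and 2 weeks is a minimum.** A charter or full protocol may time the board's review. But the interval, its purpose, the planned cadence and the stepwise halt rule are all printed here, and they do not fit together. Nothing printed requires a longer gap.
- **Prior exposure is reassuring.** The article reports no serious adverse effects in premature infants at 1.4 × 10^9 CFU twice daily for 2 weeks: 1.4 × 2 × 14 = 39.2 × 10^9 in total. Two doses at 16×, the highest multiple listed, give 2 × 16 × 0.9 = 28.8 × 10^9. This limits the weight. It does not settle the matter, because from 5× a single dose (5 × 0.9 = 4.5 × 10^9) exceeds that daily amount (2.8 × 10^9).

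**Conclusion.** The concern holds in a limited form. At the planned cadence, the 2-week spacing leaves 1 to 13 days between one group's second dose and the next group's first higher dose. It secures only a survey of the first dose. Whether a survey of the second dose comes first depends on a day that the article does not fix and on which survey schedule is followed. No passage makes board review a condition for the next level, and the halt steps do not address groups already at a higher dose.

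This rests on 14-day spacing, single-day entry of each group and entry ages of 1 to 7 days. The article gives no event rate, so no probability of harm is claimed. The change is worth making, and recruitment had not begun when the article was written.

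**What to change.** 1. **Study design and the dose-escalation section.** Count the interval from the last second dose in the preceding group. Do not enrol or dose the next level until the board has reviewed that group's week-3 survey, fixed at no later than day 21. Enrolment must wait too, because an infant entering at 7 days is due its first dose that day. If the youngest infant enters at 1 day, the spacing is 21 − 1 = 20 days plus review time: 21 days leaves 1 day for review, 24 days leaves 4.
2. **Table 2.** Mark the week-3 and week-4 surveys, to match Table 1 and the monitoring section.
3. **Stopping rules.** Add a branch: if an event is reported after a higher level has started, hold remaining doses for all five infants at higher levels (which keeps the blind) until the board rules. The repeat group receives the dose that triggered the halt. This is still needed at 21-day spacing, where the next level's first dose precedes a day-28 survey in 21/49 pairs and coincides with it in 7.
4. **Dose-escalation section.** Amend the statement that two escalations will have been performed by the time the ED is identified.

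**Cost.** At 21 days, 7 extra days per interval: 6 × 7 = 42 days over seven groups, 8 × 7 = 56 over nine. At 24 days: 6 × 10 = 60 and 8 × 10 = 80. The second escalation beyond the ED starts after the week-6 reading. Infants whose second dose is held may need replacing for the ED, up to three active infants per held level. No routine visits are added beyond Table 1.
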